# BEFRIENding for Depression, Anxiety and Social support in older adults living in Australian residential aged care facilities (BEFRIENDAS): randomised controlled trial protocol

**DOI:** 10.1186/s12877-021-02233-7

**Published:** 2021-05-12

**Keywords:** Depression, Anxiety, Loneliness, Befriending, Volunteers

## Abstract

**Background:**

This protocol describes an ongoing study of the impact of befriending on depression, anxiety and loneliness in older people living in residential aged care facilities in Australia. While systematic reviews of befriending have indicated positive benefits of befriending for people in a range of ages and settings, there have been no randomised controlled trials (RCTs) of befriending for older people living in residential aged care with depression and no studies of the cost effectiveness of befriending in residential aged care facilities (RACFs) in Australia.

**Methods and analysis:**

We are conducting a single blind pragmatic RCT comparing two groups of older people living in RACFs, one receiving an intervention consisting of weekly befriending for 4 months from a trained volunteer and the other receiving treatment as usual. Participants undergo eligibility screening for depression (GDS-15 ≥ 4) and cognitive impairment (GPCog ≥ 4) and assessments at three measurement time points: baseline prior to randomisation, 2 months post-baseline and 4 months post-baseline. The primary outcome measure is depression, and secondary outcome measures are anxiety, loneliness, social isolation and quality of life. The economic evaluation will take the form of a cost-utility analysis based on the outcome of quality of life. The primary and secondary outcomes will be analysed using negative binomial and logistic regressions utilizing the Generalised Estimating Equations approach.

**Discussion:**

To our knowledge, this is the first RCT evaluating the effectiveness of befriending on older people with depression living in residential aged care. It is expected that the befriending intervention will reduce the severity of depression symptoms experienced by older people living in residential aged care. If the intervention proves effective it may be incorporated into volunteer training programs and adopted as a way of supporting older people’s mental health.

**Trial registration:**

Trial registered with the Australian and New Zealand Clinical Trial Registry (ANZCTR) Number: ACTRN12619000676112, registered 06/05/2019 – retrospectively registered.

**Supplementary Information:**

The online version contains supplementary material available at 10.1186/s12877-021-02233-7.

## Background

Depression symptoms are experienced by many people living in residential aged care facilities (RACFs, equivalent to UK care homes and US nursing homes or long term care homes). Up to 53% of people living in Australian RACFs have been shown to have significant symptoms of depression [1, 2]. Internationally, the prevalence of depressive symptoms in people living in RACFs has been estimated to range between 11 and 78% [3]. Major depressive disorder has been estimated at 10–14.4%, which is higher than that reported within community dwelling older adults [3–6]. Despite living in a communal environment, many people living in RACFs are socially isolated [7]. Social isolation and loneliness are closely associated with symptoms of depression [8] and a recent qualitative study found that residents in RACFs attributed their sadness to loss of health and functional ability, and feeling alone in a crowd [9].

One reason for the higher prevalence of depression in RACFs may be that staff are not trained to manage depression, but studies of training staff in the detection and management of depression have met with short-term success and little sustainable change [10]. Evidence-based recommendations for the management of depression include anti-depressants or other medical treatments, psycho-education, social support, and psychological interventions [11]. In general the prescription of psychotropic medication is high among RACF residents [12, 13], but older adults have expressed concerns about using anti-depressants due to side-effects, stigma, fear of addiction and prevention of natural sadness [14]. On the other hand, psychological services can be difficult for RACF residents to access in Australia [15], as psychologists are not typically employed in Australia in such settings [16]. Furthermore, residents who are depressed or anxious are less likely to want to join in lifestyle activities by the very nature of their condition [11].

Befriending has been recommended in the National Institute for Health and Care Excellence (NICE) guidelines to assist people with moderate to severe depression who would benefit from additional social support and for those with subclinical persistent depression although there have been no studies of befriending for RACF residents [11]. Befriending is generally defined as non-directive emotional and social support which is typically administered by non-health professionals. Befriending conversations avoid health-related matters and focus on enjoyable topics of interest to both parties. The NICE guidelines recommend at least weekly befriending sessions for 2 to 6 months to gain benefit. Telephone befriending has been shown to help recipients gain confidence, re-engage with the community and become socially active again [17].

A review by Siette et al. [18] included 14 papers that focused on befriending, however none evaluated befriending in RACFs. According to that review, the training, intensity and the frequency of befriending conversations all varied in the studies reviewed [18]. In previous befriending studies, conversations were delivered one-on-one, face-to-face or by phone but could also be delivered in group support settings [19]. To date there is little evidence for the effectiveness of befriending via video calls [20]. Therefore Siette and colleagues found mixed results and recommended more specific eligibility criteria and better definitions for future studies. Despite loose definitions, befriending has been recommended as a useful complement to clinical treatments because it has potential to improve mental health outcomes. It also may be a cost effective complement to clinical treatment when administered by volunteers, although formal cost-effectiveness studies have not been published to date.

Befriending conversations can be delivered by volunteers. Research on the role of volunteers in health services has consistently shown positive effects for volunteers and older recipients of the service [21] including through: assisting with activities for socially isolated residents in aged care [22, 23]; engaging in social visits with residents in aged care [24]; and providing social support over the phone for people in the community with depression, anxiety and comorbid physical health problems [25]. When provided by volunteers, befriending has been found to significantly reduce depression symptoms in carers, those with a chronic illness, and the socially isolated, but again studies in RACF settings have not been published to date [26].

The primary aim of the BEFRIENDAS study is to test the effectiveness of befriending in relieving depression symptoms experienced by older adults living in RACFs compared with a control group receiving usual care. Secondary aims are to test its effectiveness in reducing symptoms of loneliness, anxiety, social isolation and improving quality of life. A conceptual framework or explanation for the mechanism underlying befriending is lacking in the literature, but we hypothesise that the impact of befriending on depression and anxiety is mediated by social support and reductions in loneliness (see Fig. 1).

**Fig. 1 Fig1:**
[figure not shown]
Hypothesized mediating variables between befriending and depression

## Methods and analysis

This protocol adheres to the SPIRIT 2013 checklist for recommended items to address in a clinical trial protocol. An additional file shows this in more detail (see Additional file 1).

### Study design

The BEFRIENDAS study is an ongoing single blind pragmatic RCT comparing two groups of older people living in RACFs, one receiving weekly befriending for 4 months from a trained volunteer and the other receiving treatment as usual (TAU). As few previous RCTs of befriending have been conducted, TAU is an appropriate comparator. A clustered design is not necessary because the intervention is to be delivered at the individual level and not the RACF level. Furthermore, there is no evidence that RACFs have different policies on treatment of depression. Group allocation is blinded to the assessors but necessarily un-blinded to the participant. Participants undergo eligibility screening and assessments at three measurement time points: baseline prior to randomisation (T1), 2 months after the intervention starts (T2) and at the conclusion of the intervention 4 months post-baseline (T3). Figure 2 presents the flow of the participants through the study.

**Fig. 2 Fig2:**
[figure not shown]
Flow chart of participant flow

### Participants

Participants are people over the age of 65 years living in RACFs in Australia. RACFs are a convenience sample recruited through advertisement in industry publications, word of mouth and social media. Participants in individual RACFs are identified and recruited with the assistance of a clinical care manager, lifestyle coordinator or other staff member within the RACF. The staff identify all those eligible to participate in the study using initial eligibility criteria provided below and then approach residents to gauge their interest in participating. Following instructions provided by the research team, including allowing residents to view an ‘introduction to the project’ video, the staff member explains the study to potential participants in a non-coercive way. If the resident assents, the research assistant meets with them either face-to-face or remotely via telephone or video call to conduct further eligibility screening, confirms eligibility, provides additional information about the study and gains written informed consent to proceed. All consent is provided by participants not by proxies.

#### Initial eligibility criteria used by staff to identify eligible residents

Cornell Scale for Depression in Dementia (CSDD) [27] score of 8 or greater as assessed by RACF staff (no longer than 6 months prior) orPsychogeriatric Assessment Scale – Cognitive Impairment Scale (PAS-CIS) [28] score equal to or less than 10, as assessed by RACF staff (no longer than 6 months prior) orClinical judgement of clinical care manager indicating significant depression or anxiety symptoms.

#### Further eligibility screen conducted by research assistants to confirm eligibility

Geriatric Depression Scale 15-item (GDS 15) [29] score of 4 or greater as assessed by the research assistant.General Practitioner Assessment of Cognition (GPCOG) [30] score of 4 or greater as assessed by the research assistant.

Residents who are unable to give informed consent, have progressive, unstable medical or neurological illness, a diagnosis of dementia or who are under the age of 65 years are excluded from the project.

Volunteers administer the befriending intervention and participate in qualitative evaluation of the experience. Volunteers are a convenience sample recruited via volunteer recruitment websites, social media advertisement, word of mouth and through advertisements in industry newsletters. Volunteers are eligible to participate if:
over 18 years and have a valid police checkhave an up to date influenza immunisationassessed as suitable (according to availability, conversation skills and attitudes) in an interview with the volunteer coordinatoravailable for at least 6 months of volunteeringable to travel to the RACF where appropriatewilling to participate in training and ongoing supervision.

#### Patient and public involvement

The befriending intervention is a manualised and structured intervention (manuals available from corresponding author). The topics of conversation are guided by the resident participants and volunteers. A project advisory group will be established to guide the dissemination of the findings and to advise on how the befriending model can be translated into practice in RACFs. This advisory group will consist of staff representatives from RACFs, residents from RACFs and family members of residents from RACFs.

### Sample size

We are aiming for a clinically significant change of greater than two points in the GDS. Based on the average effect size of 0.27 for short term befriending outcome studies of mostly older adults with depression in primary care settings, it is estimated that with data collection spread over a three-year period, and allowing for a higher than usual dropout rate of 20% given low life expectancy among RACF residents, recruiting 172 participants per study arm (total of 344 participants) would achieve 80% power, with a statistical significance of 0.05. It is anticipated that each volunteer recruited may only befriend one participant, so a total of over 500 volunteers will be recruited throughout the study. Recruitment strategies to achieve the sample include wide ongoing advertisement and presentations in industry meetings and publications, monitoring quotas and widening locations where needed.

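### On the inputs printed in the article, 172 recruited per arm does not give 80% power for a comparison of two means; it gives about 61%

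*Protocol article*

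**What the plan says.** The Sample size section of the protocol article gives every input in one sentence. The effect: "Based on the average effect size of 0.27 for short term befriending outcome studies of mostly older adults with depression in primary care settings". The attrition: "allowing for a higher than usual dropout rate of 20% given low life expectancy among RACF residents". The result: "recruiting 172 participants per study arm (total of 344 participants) would achieve 80% power, with a statistical significance of 0.05". It does not give the sidedness of the test, the type of test, a standard deviation or a correlation between measurements.

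Elsewhere, the Study design section describes two individually randomised groups and rejects a clustered design. The Randomisation section uses blocks of two, so the arms are equal. The Data analysis section plans negative binomial and logistic regressions by GEE with an exchangeable working matrix. Table 1 places the GDS 15 at screening, 2 months and 4 months. The Sample size section does not refer to any of these analysis features.

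**The concern.** The sentence says that the recruited number already allows for dropout. The number of evaluable participants must then be smaller than 172 per arm and still give 80% power for an effect of 0.27. A standard calculation needs more than 172 evaluable per arm before anyone is lost, so the printed output is too small for its printed inputs.

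This is the power claim for the primary outcome, and the mismatch is in the favourable direction. If no unstated gain in precision lies behind it, the chance of missing an effect of 0.27 is about 39% (100 - 61), not 20%. A null result would then be read as coming from a better powered trial than was run.

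**Working it through.** **Inputs, all from the Sample size section:** d = 0.27; significance level 0.05; power 80%; dropout 20%; 172 recruited per arm. Equal arms. Sidedness is not stated, so two-sided is taken as the main case and one-sided is also tried.

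**1. Evaluable number needed, two-sided.**
n per arm = 2 x (1.960 + 0.842)² / 0.27² = 215.3, so 216 (217 with the t distribution). This already exceeds 172.

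**2. Allowance for dropout.**
215.3 / 0.8 = 269.2. Rounding up to 216 first gives 216 / 0.8 = 270 recruited per arm, 540 in total (272 and 544 with the t distribution).

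**3. Attempts to reproduce 172.**

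| Route | Per arm |
|---|---|
| Two-sided, no dropout | 216 |
| Two-sided, divided by 0.8 | 270 |
| Two-sided, multiplied by 1.2 | 260 |
| Two-sided, multiplied by 0.8 | 215.3 x 0.8 = 172.3 |
| One-sided, no dropout | 170 (171 by t) |
| One-sided, divided by 0.8 | 213 (214 by t) |
| Two-sided, baseline correlation 0.6, divided by 0.8 | 215.3 x (1 - 0.36) / 0.8 = 172.3 |

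Two routes give 172.3: an inverted dropout adjustment, and a correct adjustment after an unstated baseline correlation of 0.6. They coincide because 0.64 / 0.8 = 0.8. The one-sided route comes close only by ignoring the dropout that the sentence says was allowed for.

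**4. Power at the stated recruitment.**
Completers per arm: 172 x 0.8 = 137.6. Two-sided power = Φ(0.27 x √(n/2) - 1.960).

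- 137.6 per arm: Φ(2.240 - 1.960) = 61.0% (60.7% by t).
- 172 per arm, no dropout: Φ(2.504 - 1.960) = 70.7% (70.4% by t).
- 137.6 per arm, one-sided: Φ(2.240 - 1.645) = 72.4% (72.2% by t).

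**5. Effect detectable with 80% power.**
(1.960 + 0.842) x √(2 / 137.6) = 0.338 (0.339 by t), so about 0.34.

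**6. What an unstated gain in precision could do.** These are normal approximations with 137.6 completers per arm and an assumed correlation r; the article gives no value for r.

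- 4-month score only, baseline-adjusted, variance factor 1 - r²: 73% at r = 0.5 and 80% at r = 0.6.
- Average of the 2- and 4-month scores, baseline-adjusted, with a common r and an equal effect at both visits, variance factor (1 + r)/2 - r²: 89% at r = 0, 85% at r = 0.25, 89% at r = 0.5, 92% at r = 0.6.
- Average change from baseline over both visits, same assumptions: 73% at r = 0.5 and 82% at r = 0.6.

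For 80% power the variance factor must be no more than 137.6 / 215.3 = 0.639.

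**The case against.** The strongest reply is that 61% is not the power of the planned analysis. It compares two means at a single time point and ignores baseline, whereas the Data analysis section plans a GEE over repeated measurements. A baseline-adjusted average of the two follow-up visits would give about 85% or more for any common correlation, if the effect were equal at both visits. This stands as a limit on the figure: the article does not establish one actual power for the trial, and a baseline correlation of about 0.6 is not the only way to reach 80%. It does not rescue the sentence, which presents 80% as following from the effect size, significance level and dropout alone, with no correlation, averaging or variance reduction.

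A second reply is that a condensed article may leave such details to a fuller document. That would answer a complaint about an omission. Here, printed inputs and a printed output disagree.

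A third is that the section also aims for a change of more than two GDS points. With a detectable effect of 0.339 SD, 138 per arm has 80% power for a two-point difference for any SD up to 2 / 0.339 = 5.9. This is fair, and the 39% risk of a miss applies only to an effect of 0.27. But 0.27 is the effect on which the section bases its number.

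Two stronger inferences are tempting and unsupported. A reader might conclude that the sample was shrunk for dropout by mistake. The match with 215.3 x 0.8 suggests this, but the calculation with a correlation of 0.6 gives the same number. A reader might also take the statement "so a total of over 500 volunteers will be recruited throughout the study" as a trace of a true target near 540. The article offers control participants a befriender after their four months and replaces volunteers who leave, so more than 500 volunteers can fit 344 participants.

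**Conclusion.** The point holds. For a comparison of two means on the printed inputs, 172 recruited per arm does not give 80% power. Two-sided power is about 61% after 20% dropout, with 80% power only for an effect of about 0.34; about 216 evaluable, or about 270 recruited, per arm would be needed for 0.27. Neither a one-sided test (about 72%) nor the absence of dropout (about 70%, two-sided) closes the gap alone; both together would, but the sentence says that dropout was allowed for.

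This rests on equal arms, 0.27 being a standardised mean difference, and no gain from baseline or repeated measurements. It does not show that the planned GEE analysis has 61% power, nor how the figure 172 arose. It shows that the stated 80% does not follow from what the section states.

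**What to change.** Restate the sentence in the Sample size section and leave enrolment as it is. State whether the test is one- or two-sided, and the evaluable number expected (about 138 per arm). Then do one of the following:

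- If no gain in precision was assumed, give the power that the inputs deliver. For example: 344 recruited (172 per arm), about 138 per arm after 20% dropout, gives about 61% power for an effect of 0.27 and 80% power for an effect of about 0.34, two-sided 0.05.
- If the 80% relies on baseline adjustment or on the repeated measurements in the GEE, state the contrast and the assumed correlation that produce it. For the 4-month score alone with baseline adjustment, r = 0.5 gives about 73% and r = 0.6 about 80%.

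The cost is one corrected paragraph. Under the first option the stated power becomes less favourable.

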### Randomisation

Following the baseline assessment, participants are randomly allocated to the befriending intervention group or the TAU control group. Relevant concomitant care and interventions such as psychological interventions or anti-depressants are noted and considered treatment as usual. Randomisation is managed by a trial statistician who is not directly involved in the study. A computer-generated random sequence available to the trial statistician, but no other research staff, is used to produce random allocation using a randomised permuted block design with block size of two in order to maintain approximately balanced randomisation throughout the trial. Randomisation is provided to an un-blinded researcher via email to verify that the correct allocation has taken place. The un-blinded researcher notifies the participants about their allocation and arranges for the intervention to begin. Research assistants conducting the assessments are blinded to group allocation.

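### Fixed permuted blocks of two leave the second allocation of each pair certain to anyone who knows the order and the first, which weakens allocation concealment and assessor blinding

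*Protocol article*

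**What the plan says.** The protocol article, under Randomisation, describes a "randomised permuted block design with block size of two in order to maintain approximately balanced randomisation throughout the trial". It names no other block size, no random variation of size and no stratification by facility. The ratio is 1:1, since the Sample size section plans for "recruiting 172 participants per study arm (total of 344 participants) would achieve 80% power, with a statistical significance of 0.05".

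Custody of the list is described as "A computer-generated random sequence available to the trial statistician, but no other research staff". Individual allocations then leave the statistician: "Randomisation is provided to an un-blinded researcher via email to verify that the correct allocation has taken place", and "The un-blinded researcher notifies the participants about their allocation and arranges for the intervention to begin". Allocation follows the baseline assessment.

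Study design calls the trial an "ongoing single blind pragmatic RCT comparing two groups of older people living in RACFs" and adds: "Group allocation is blinded to the assessors but necessarily un-blinded to the participant". Under Participants, "Participants in individual RACFs are identified and recruited with the assistance of a clinical care manager, lifestyle coordinator or other staff member"; one of the initial eligibility routes is the care manager's clinical judgement. Research assistants then confirm eligibility with the GDS 15 and GPCOG. Under Data collection and management, blinded research assistants collect the outcomes by structured interview.

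**The concern.** In a block of two there are only two orders, AB and BA, so knowing the first allocation gives the second. Keeping the list with the statistician hides the list, but it does not prevent inference from allocations already made, and in this trial those are partly visible. Residents know their arm, and weekly sessions take place at the facility or by phone or video, so facility staff can plausibly tell who has a befriender. The same staff decide whom to approach and when. The block size is also published while the trial is described as ongoing.

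Two things are at stake:

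- **Selection.** A staff member who expects the next allocation can bring a particular resident forward or hold one back. Analysis cannot repair this reliably afterwards.
- **Assessor blinding.** The primary outcome, the GDS 15, is obtained by interview from a resident who knows the arm. If a resident mentions a befriender, the assessor learns that resident's arm. If the assessor also knows the order and the pairing, the pair-mate's arm follows.

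**Working it through.** The plan states no figure for predictability, so there is none to reproduce. The check is exact arithmetic on the stated design, followed by a comparison with other block sizes.

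**Inputs from the protocol article**
- Block size 2, fixed (Randomisation).
- 1:1 allocation, 172 per arm, 344 in total (Sample size).

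**Assumptions**
- The observer knows the trial-wide order, the block position and the preceding allocations. This is the worst case.
- The comparison block sizes are chosen for illustration. The protocol names none.

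**Share of allocations that are certain.** In a 1:1 block of size 2m, the expected number of allocations already determined at the end of the block is 2m/(m+1). Dividing by 2m gives a share of 1/(m+1).
- Block of 2 (m = 1): 1/2, and 0.5 × 344 = 172 allocations.

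**Share guessed correctly.** The best strategy is to guess the arm with more places left in the block, or either arm when they are level (the Blackwell-Hodges convergence strategy).
- Block of 2: the first allocation is a coin toss and the second is certain, so 0.5 × 0.5 + 0.5 × 1 = 0.75. That is 0.75 × 344 = 258 correct guesses, against 172 with no information.

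**Comparison**

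| Block scheme | Certain | Guessed correctly | Largest imbalance |
|---|---|---|---|
| Fixed 2 (as planned) | 50% | 75% | 1 |
| Fixed 4 | 33.3% | 70.8% | 2 |
| Fixed 6 | 25.0% | 68.3% | 3 |
| Fixed 8 | 20.0% | 66.6% | 4 |
| Random 4/6/8, undisclosed | about 2% | about 68.0% | 4 |

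The fixed-size rows are exact. The last row is simulated over sequences of 344. Its 2% is for an observer who knows which sizes are in use and has seen every earlier allocation, but not the size of each block. The largest imbalance is half the largest block.

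Two results follow. Size two is the worst case at 1:1 on both measures of predictability. The gain from varied blocks lies mainly in certainty, which falls from 50% to about 2%; the guess rate falls by only about 7 percentage points (75% − 68%).

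**What a disclosure reveals.** One known allocation determines the other member of the same pair and nothing else. The neighbour on the other side belongs to a different block and stays at 50:50.

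**The case against.** The strongest reply is that the headline figures need more knowledge than anyone who selects or assesses residents is shown to have. There is one sequence, held by a statistician not directly involved in the study, and no stratification by facility is stated. Facility staff would see allocations only at their own site. If the two members of a pair come from different facilities, a visible allocation says nothing about the next local resident. This stands: 172 of 344 and 75% are upper bounds.

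Other parts also stand:

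- The un-blinded researcher sees every allocation, and a reader might infer that this person could steer enrolment. The protocol gives the researcher no role in identifying, approaching or consenting residents, so no such route is documented.
- Allocation follows consent and baseline, and entry needs GDS 15 and GPCOG scores taken by a research assistant. Staff judgement alone cannot enrol anyone. Controls are offered a befriender after four months, which weakens the motive to steer. These features reduce selective approach but do not remove it.
- A reader might call the trial open-label, or say that each unblinding does double damage. The document says single blind with blinded assessors. The pair-mate is revealed only to an assessor who also knows order and block position, and nothing says that assessors do.
- Varied blocks do not make allocation unguessable; about 68% of guesses would still be right.

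None of this supports size two. The stated purpose is approximate balance, and larger or varied blocks achieve that as well.

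**Conclusion.** The design weakness holds. Fixed 1:1 blocks of two are the most predictable permuted blocks available, and the trial's setting gives that predictability possible routes to harm: un-blinded participants, facility staff with discretion over whom to approach, and an interview-based primary outcome. For an observer with order, block position and the preceding allocation, up to 50% of allocations (at most 172 of 344) are certain and 75% can be guessed. Concealment and assessor blinding are weakened.

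The practical size depends on how often consecutive randomisations come from one facility, and the protocol does not give this. It would be near the upper bound if pairs usually share a site and small if they rarely do. A reader might infer that concealment has failed or that the results are biased. The documents do not support that: the list itself is held independently, and no misuse is shown. This is a conditional risk that should be reduced while recruitment continues.

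**What to change.** For all remaining participants, the independent statistician should generate a new list with randomly varying block sizes, for example 4, 6 and 8, starting after a completed pair. The sizes should not be disclosed to recruiting or assessing staff, or in documents that they can read. The trial report should state how many participants were randomised under blocks of two.

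The cost is a new list, a short amendment and a possible final imbalance of up to 4 participants among 344. The benefit depends on how many participants are still to be randomised, which the article does not state. Allocations already made under blocks of two are unaffected.
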